### Process evaluation

The process evaluation assesses the extent to which the CATI intervention programme is performed according to study protocol and gives insight into barriers and facilitators in executing the different components of the intervention programme. Data will be collected on time that is spent by the pharmacists in executing the intervention programme and the intervention modules that are selected and performed. Data on these topics will be collected using an administration form. In addition, semistructured interviews will be held with the participating pharmacists at the end of the study in order to record experiences and opinions on the intervention programme. The presence of possible contamination will also be assessed by interviewing the pharmacy technicians. Furthermore, after the follow-up consult participants will fill out a questionnaire to evaluate the different components of the intervention programme.

### Economic evaluation

Both a cost-effectiveness analysis and a cost-utility analysis will be performed according to the intention-to-treat principle. Missing cost and effect data will be imputed using Multiple Imputation by Chained Equations (MICE) [47]. To account for the skewed distribution of costs Predictive Mean Matching will be used in the MICE procedure. The number of imputed datasets will be increased until the loss of efficiency is less than 5% [48]. The results of the imputed datasets will be pooled according to Rubin’s rules. Bivariate regression analyses will be used to estimate cost and effect differences while adjusting for potential confounders and maintaining the correlation between costs and effects. Incremental Cost-Effectiveness Ratios (ICERs) will be calculated by dividing the mean difference in total societal costs by the mean difference in effects. Bias-corrected and accelerated bootstrapping with 5000 replications will be used to estimate 95% confidence intervals around cost and effect differences, and to estimate the uncertainty surrounding the ICERs which will be graphically presented on a cost-effectiveness plane [49]. Cost-effectiveness acceptability curves will be estimated in which the probability that the intervention programme is cost-effective in comparison to usual care is plotted on the y-axis, while the willingness-to-pay per incremental unit of effect is plotted on the x-axis [50].

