### Study design

A parallel-group randomised controlled trial will be performed in 13 community pharmacies including 156 patients (Fig. 1). Patients will be randomly assigned to the intervention or the control condition. Patients in the intervention condition will receive the CATI intervention programme performed by the pharmacist, in addition to usual care (further described below in 'Control condition'). The effectiveness of the CATI intervention programme will be measured during a 9-month follow-up. See Additional file 1 for an overview of the Standard Protocol Items: Recommendations for Interventional Trials (SPIRIT) 2013 checklist items [26]. See Additional file 2 for the SPIRIT diagram of the trial procedure.

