### Statistical analyses

Descriptive statistics will be used to characterise the study population. Dropout and loss to follow-up will also be described. The effect analyses will be performed according to the ‘intention-to-treat’ and ‘per-protocol’ principles. Linear and logistic mixed-model analyses will be used to assess the effect of the intervention programme by comparing the differences between the intervention and the control conditions. Mixed-model analysis is needed in order to take into account clustering on pharmacy level and repeated measurements in one patient. Adjustments will be made for possible confounders such as gender, age and education level. The researcher will be blinded during data analyses.

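### The economic evaluation's imputation stopping rule leaves results that shift visibly with the random seed, and the section does not say how pharmacy enters the imputation, regression or bootstrap

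*Protocol article*

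**What the plan says.** **Imputation.** Economic evaluation uses chained equations with predictive mean matching. The number of datasets is governed by one criterion: "The number of imputed datasets will be increased until the loss of efficiency is less than 5" per cent. No number and no minimum is given. On pooling, it says: "The results of the imputed datasets will be pooled according to Rubin’s rules".

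**Model and intervals.** "Bivariate regression analyses will be used to estimate cost and effect differences while adjusting for potential confounders", with the correlation between the two preserved. "Bias-corrected and accelerated bootstrapping with 5000 replications will be used to estimate 95% confidence intervals around cost and effect differences". The unit of resampling is not stated. The cost-effectiveness plane and the acceptability curves are planned outputs.

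**Pharmacy.** Statistical analyses, writing of the effect analyses, says: "Mixed-model analysis is needed in order to take into account clustering on pharmacy level and repeated measurements in one patient". Study design gives the numbers: "A parallel-group randomised controlled trial will be performed in 13 community pharmacies including 156 patients". According to the Discussion, patients are randomised individually, so both conditions run in every pharmacy. According to Intervention condition, the pharmacist delivers the programme.

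**The concern.** There are two separate points about the same section.

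1. A 5% efficiency criterion looks strict but is not. It limits how much variance the point estimate loses to a finite number of imputations. It was not designed to make intervals and acceptability probabilities repeatable. Two analysts following the plan exactly could report noticeably different probabilities that the programme is cost-effective.

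2. The article calls a mixed model necessary for pharmacy clustering. It then describes cost and effect estimation in the same patients, down to the number of bootstrap replications, without mentioning pharmacy. If the programme's cost or effect varies between pharmacists, patient-level intervals would overstate precision. Cost-effectiveness is part of the trial's stated aim, so these intervals will be read.

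**Working it through.** Economic evaluation contains no computed figure to reproduce. Its one numerical input here is the 5% threshold.

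**Imputation rule**

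Relative efficiency with m datasets is 1/(1 + FMI/m). A loss below 5% means (FMI/m)/(1 + FMI/m) < 0.05, which gives FMI/m < 1/19, or m > 19 × FMI.

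The FMI is not in the document. The nearest figure is the loss to follow-up of about 30% in Sample size, used here as an assumption. At FMI 0.30:

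- m = 5: 0.06/1.06 = 5.66%, rule not met.
- m = 6: 0.05/1.05 = 4.76%, rule met.

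| Assumed FMI | First m meeting the rule | Re-run SD of pooled difference, √(FMI/m), in SE |
|---|---|---|
| 0.1 | 2 | 0.224 |
| 0.2 | 4 | 0.224 |
| 0.3 | 6 | 0.224 |
| 0.4 | 8 | 0.224 |
| 0.5 | 10 | 0.224 |
| 0.7 | 14 | 0.224 |

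The last column is constant because the rule fixes FMI/m. It can never exceed √(1/19) = 0.229. Two independent runs differ with an SD of √2 × 0.224 = 0.32 SE.

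*Acceptability probability.* Suppose the true value is 84%, that is Φ(1). The 95% range over seeds is Φ(1 ± 1.96 × √(FMI/m)). At FMI 0.30:

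- m = 6: Φ(1 ± 0.438) = 71% to 92%.
- m = 50: √(0.3/50) = 0.077, so Φ(1 ± 0.152) = 80% to 88%.

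Simulation of a true 80% gave a 5th to 95th percentile range of 0.68 to 0.89 at m = 6 and 0.76 to 0.84 at m = 50.

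*Compared with bootstrap noise.* With 5000 replications, the simulation error of an 84% probability is √(0.84 × 0.16/5000) = 0.5 percentage points. The imputation step at m = 6 contributes about φ(1) × 0.224 = 0.242 × 0.224 = 5.4 points.

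*Interval width* (100,000 simulated sets, FMI 0.30). The mean half-width is 2.06 SE at m = 6 and 1.96 SE at m = 100. The coefficient of variation (CV) of the half-width is 12.5% at m = 6 (5th to 95th percentile 1.74 to 2.55 SE) and 3.1% at m = 50. The mean is therefore little affected, and slightly on the wide side; it is the value in a single run that is unstable.

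**Pharmacy clustering**

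The document gives no intracluster correlation (ICC) and no between-pharmacist variance of the effect, so both are assumed. Trials with 13 pharmacies of 12 patients (156/13 = 12) and 1:1 individual randomisation were simulated. The SE that ignores pharmacy was compared with the true SD of the estimate. Variances are fractions of the patient-level variance.

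| Scenario | Naive SE / true SD | Coverage of 95% interval |
|---|---|---|
| Constant effect, arms balanced within pharmacy, ICC 0.01–0.20 | 1.02–1.10 | 95.4%–96.5% |
| Constant effect, no stratification, ICC 0.01–0.20 | 0.97–1.01 | 94.0%–95.1% |
| Effect variance 0.05–0.10, either allocation, ICC 0.01–0.20 | 0.88–1.02 | 91.6%–94.9% |
| Effect variance up to 0.20 | down to about 0.81–0.83 | about 89% |

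Effect variances of 0.05, 0.10 and 0.20 mean that the true effect varies between pharmacists with an SD of √0.05 = 0.22, √0.10 = 0.32 and √0.20 = 0.45 patient SDs.

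*Remedies* (ICC 0.1, effect variance 0.1, balanced arms). Fixed pharmacy indicators with model-based SEs lower the ratio from 0.93 to 0.88, with coverage 91.4%, because they remove level differences but not variation in effect. Pharmacy-clustered SEs with t on 13 − 1 = 12 degrees of freedom bring coverage back to about 95%.

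**The case against.** **Silence is not exclusion.** The section is one paragraph of a journal article. The imputation predictors, the list of confounders and the resampling unit may sit in a fuller plan, and the sentence calling a mixed model necessary is written for the effect analyses. This stands: a reader might infer that clustering will be ignored, and the document does not say so. What remains is an inconsistency to reconcile, in a section that otherwise specifies its methods closely.

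**Mis-sized intervals.** A reader might infer that intervals are wrong by a cluster-trial design effect. That does not follow, because randomisation is within pharmacies. Excess width needs balance within pharmacy, and Randomisation does not state stratification by pharmacy. Excess narrowness needs an effect that varies between pharmacists, for which no size is given. The two errors can also cancel: ICC 0.20 with effect variance 0.05 and balanced arms gave a ratio of 1.02.

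**About six datasets.** A reader might take 6 as the plan's number. It is not; it rests on equating FMI with loss to follow-up. The true FMI could be lower if observed data predict the missing values well. It could be higher, since total costs combine several questionnaires and quality-adjusted life years need utilities at four time points. The re-run error does not depend on this choice.

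**Validity.** Rubin's rules already allow for finite m, and the 5% rule is prespecified and cited. Both are true. The rule also does not forbid using more datasets, but as worded it allows stopping at the first m that qualifies. Fifty is one reasonable minimum, not the only one: a 5% CV of the SE needs 1 + ½(0.30/0.05)² = 19 datasets at FMI 0.30 and 51 at FMI 0.50.

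**Conclusion.** The imputation point holds on the rule as written and does not depend on the assumed FMI. Stopping at the first qualifying m leaves re-run error of about 0.22 SE. That is enough to move an 84% acceptability probability between about 71% and 92% by seed (the percentages are worked at FMI 0.30). It is a fault of reproducibility, not of interval validity.

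The clustering point holds as an inconsistency with conditional consequences. Under assumed variances that the document does not supply, intervals are about right or up to about 10% too wide if pharmacies differ only in level. They are roughly 2% to 20% too narrow if the programme's effect varies between pharmacists; the upper end needs an effect variance of about 0.2.

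Both points concern the economic evaluation. The primary MARS-5 analysis, whose model does address pharmacy, is not affected. A correction is worth making because it is cheap.

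**What to change.** 1. **Number of imputations.** Replace the 5% rule with a fixed minimum, for example 50, or with a Monte Carlo error limit. A limit of 0.1 SE on the pooled difference means FMI/m ≤ 0.01, so m ≥ 30, 50 or 70 at FMI 0.3, 0.5 or 0.7. State and report the seed. The cost is computing time only.

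2. **Pharmacy.** Include pharmacy in the imputation model. For inference, resample at pharmacy level, or use pharmacy-clustered standard errors with a small-sample correction (t on 12 degrees of freedom), or fit a bivariate mixed model with a random treatment effect by pharmacy. Pharmacy indicators alone with model-based standard errors are not sufficient. Show the patient-level analysis beside it, because 13 clusters make the pharmacy-level version somewhat noisy. If pharmacy is left out on purpose, give the reason and reconcile it with Statistical analyses. The cost is a few lines of analysis wording; no data collection changes.

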## Discussion

This study is expected to add evidence to the (cost-)effectiveness of a patient-tailored, theory-driven, pharmacist-led intervention programme as compared to usual care in patients using antihypertensive medication. The intervention programme includes a variety of tools to support patients to overcome barriers to adherence, thereby improving medication adherence. It is expected that patients will be encouraged to adjust their adherence behaviour. This will be achieved by learning from the provided information, following the pharmacists’ advice and by using supporting aids. In addition, performing an action plan and discussing the use and results of the plan at a follow-up visit may increase these achievements. Moreover, the personal attention of the pharmacist towards the patient is expected to be a stimulating factor for behavioral change.

A strength of this study is the theory-driven and patient-tailored approach of the intervention programme. All patients have their own medication intake behaviour, experience their own problems and barriers to adherence and have their own needs. By focussing on identifying patients’ barriers in the initial phase and subsequently addressing these barriers by providing specific information and advice to patients, the patient-tailored approach is applied. Moreover, encouraging patients to self-regulate their medication intake behaviour by overcoming specific barriers will lead to the improvement of medication adherence. In addition, this intervention programme has been developed for patients non-adherent with their antihypertensive medication, and will not unnecessarily be addressed to the general population of antihypertensive medication users. Another strength of the study is the execution of a pilot study which resulted in improving and finalising the intervention programme. The study will be conducted in daily clinical practice. This increases the feasibility of implementing the CATI intervention programme in a community pharmacy setting on a large scale. Furthermore, alongside the study a process evaluation will be performed. This will enable us to assess the implementation fidelity and add to a careful interpretation of the results of the study.

The MARS-5 questionnaire has been selected as the primary outcome for this study. Two studies showed poor sensitivity results of the MARS-5 questionnaire [51, 52]. This could be a limitation of this study. An explanation for these results could be the use of the Medication Possession Ratio as a reference standard. This method calculates the extent to which patients refill their medication, rather than calculating the extent to which patients take their medication. Despite these results, the MARS-5 questionnaire has several advantages. First, the questionnaire performs well on other psychometric properties. Second, the response scale allows patients to be graded in terms of the frequency with which they engage in non-adherent behaviours. Third, the questionnaire can distinguish between patients with intentional and unintentional medication non-adherence. Lastly, this questionnaire is relatively short and easy to use. Another limitation of this study is that, due to the nature of the intervention, it is not possible to blind the researcher, patients, pharmacists or pharmacy technicians to the group allocation of participants. To minimise possible ascertainment bias before data collection participants were informed about being randomised into one out of two programmes, with either three blood pressure measurements or two consults and three blood pressure measurements. Moreover, to minimise possible ascertainment bias after data collection, the researcher will be blinded during data analyses. A final limitation of this study is that due to performing the randomisation at the individual level both the intervention and the control conditions will be conducted in one pharmacy which can lead to contamination. To minimise contamination within one pharmacy, the intervention programme and blood pressure measurements will be performed by a pharmacist, whereas the blood pressure measurements in the control condition will be performed by a pharmacy technician; previously, pharmacy technicians had been instructed to perform no activities other than usual care during the three blood pressure measurement visits.

If the CATI intervention programme is feasible and effective, it could potentially be extrapolated to other groups of patients in whom medication non-adherence is also a problem. The information gained from this study may prove useful for policy-makers, health care providers, and researchers who are in the process of improving adherence with the use of (cardiovascular) medication.

### Trial status

The inclusion of patients and the collection of data started in March 2016. The inclusion of patients ended in the third quarter of 2016. Results will be expected in 2017.

## Abbreviations

BMQ: Beliefs about Medicines Questionnaire
BP: Blood pressure
Brief IPQ: Brief Illness Perceptions Questionnaire
CATI: Cardiovascular medication non-Adherence Tailored Intervention
MARS-5: Medication Adherence Report Scale
QBS: Quick Barrier Scan
QoL: Quality of Life
SFK: Foundation for Pharmaceutical Statistics
SPIRIT: Standard Protocol Items: Recommendations for Interventional Trials
TIG: Tailored Intervention Guide
